#### Development of FFQ score

The FFQ score will be developed using the participant’s dietary intake captured by the FFQ (**Fig 1**). The scoring system will be undertaken similar to the methods used by Framingham and INTERHEART. Briefly, using a random sub-sample of the study population (e.g., 1/3) as a test group, the intake of all 27 food items for each participant will be converted into tertiles, where 1^st^, 2^nd^, and 3^rd^ tertiles represent low, moderate, and high intake for the food item. The association between tertile scores for each of the 27 food groups and hypertension will be individually evaluated in 27 multiple variable regression models in the test group, adjusted for common covariates (e.g., sex, age, etc.). The beta-coefficients for the food item (rounded to the nearest integer) in each multiple variable model, that is significant (p<0.05), will be used as a ‘weight’ to quantify the individual food item’s contribution to hypertension risk. These food tertiles and their weights with then be used to calculate FFQ scores in the other 2/3 of the study population (i.e., validation group) for each individual and then regressed against measures of hypertension. Correlation matrices and forward stepwise regression models will be checked and used to minimise the effect of correlated food items. If the FFQ score is valid, a significant association will be observed between the FFQ score and measures of hypertension.

*Phase 2*. ***Acceptability assessment of the FFQ*.** A feasibility trial to test the acceptability of the refined FFQ and gather information on modifications to improve ease of use and future implementation in Nigerian clinics will be conducted (**Fig 1**). The FFQ will be administered to clinical patients (n = 50) once to collect their dietary intake and feedback to assess the acceptability of the FFQ. Acceptability will be evaluated by qualitative feedback on indicators of the (i) process (e.g., proportion interested, started, completed FFQ), (ii) resource (e.g., time to complete and review, rated performance on handheld devices), and (iii) data management (e.g., suitability of user interface, data storage and analyses) endpoints [30]. Ten questions, 5-item Likert-scale questions, such as “strongly disagree, disagree, neutral, agree, or strongly agree”. The ratings for each of the 10 questions will be used to generate both individual participants’ acceptability ratings as well as an overall acceptability score from all participants.

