## Abstract

Contrary to North America and Europe, the prevalence of hypertension is rising in West Africa. With a transition from whole foods to processed foods in Nigeria, diet plays a key driver of hypertension. To combat this, the national nutritional guidelines in Nigeria were implemented, but their translation into actionable tools for clinicians remains a challenge. Currently, there are no simple dietary assessment tools that are concise and suitable to be incorporated into clinical care without requiring extensive data analysis while still providing personalised dietary support to their patients. This study aims to deliver a clinically tested and validated short dietary assessment tool for clinicians, patients, and researchers across Nigeria to provide personalised dietary advice for patients with hypertension. The study will be conducted in two phases: Phase 1 (n = 75) will investigate the feasibility of the short FFQ and its agreement with 24-hour dietary recalls (3x) in a clinical setting in Nigeria. During the analysis of Phase 1 data, a scoring system will be developed based on the associations between individual food items in the FFQ and measures of hypertension. Phase 2 (n = 50) will assess the acceptability of the FFQ and validate the association between the FFQ score and hypertension. **Expected outcomes:** The development of a clinically tested and validated short food frequency questionnaire that will be ready to use by clinicians, patients, and researchers across Nigeria to support the prevention and management of hypertension. This study will contribute to knowledge on dietary assessment and hypertension prevention by developing a validated and acceptable FFQ, which will be valuable for clinicians and researchers for personalised dietary recommendations to combat hypertension in Nigeria.

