### Sample size and sampling technique

The targeted sample size for this study was determined by previous studies evaluating the agreement between food frequency questionnaires (FFQs) and 24-hour dietary recalls. These studies have found correlation coefficients (r) ranging from 0.3 to o.7, indicating moderate to strong agreement between the two dietary assessment methods [23–26]. Based on this evidence, a modest correlation coefficient of *r* = 0.5 is considered a good indicator of validity for determining the sample size needed to evaluate the agreement between our clinical FFQ and 24-hour recall [27]. Using G*Power software [28], a priori sample size calculation was conducted for a two-tailed correlation analysis with statistical power = 0.8, alpha = 0.05, and r = 0.5. The analysis indicated that a minimum of 29 participants would be needed to detect a significant correlation between the FFQ and recall measures.

In addition, recent evidence suggests that a sample of approximately 13 participants is sufficient to reach saturation in qualitative studies with a small number of clear objectives (*See Section 3*.*4*.*2*: *Feasibility assessment of FFQ*) [29]. Therefore, the planned sample of 29 participants will be sufficiently powered to evaluate the qualitative evidence and feedback. Nonetheless, to account for an anticipated dropout rate of 20% as well as to accommodate any potential missing/incomplete data, the target sample size will be increased to 50 participants (**Fig 2**) [30, 31]. Furthermore, 25 healthcare professionals consisting of nurses, dietitians, and clinicians at RSUTH will be purposely recruited to provide qualitative feedback on the food frequency questionnaire.

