#### Validation and reproducibility of the FFQ

The FFQ will be administered to clinical patients (*n* = 50) twice (i.e., first and third visits) to quantify the intake of food items. Additionally, an inconsecutive three (3) repeated 24HR, including two weekdays and one weekend day, will be used to collect dietary information from the clinical patients for the past 24 hours using the multiple-pass method [21, 22] at the time of visits and intervals between the two FFQs administrations (**Fig 1**). The reproducibility of the FFQ will be assessed by measuring the level of agreement between the two administrations of the FFQ. Furthermore, the validation will be assessed by evaluating the agreement level between the FFQ and the average of the three 24-hour recalls [32, 33]. Healthcare professionals are not involved in the patient FFQ validation stage.

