#### Non-dietary data collection

In phases 1 and 2, in addition to dietary intake, socioeconomic and demographic data such as gender (sex), age, education, and level of physical activity will be collected using a structured questionnaire from the clinical patients. The blood pressure and anthropometric data (such as weight and height) will be measured using a standard procedure from each clinical patient, and the average will be calculated and used. Body mass index (BMI) will be calculated using weight in kilograms by height in meters squared. Hypertension will be defined as SBP ≥ 140mm Hg and DBP ≥ 90mm Hg or on antihypertension medication [34].

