The limitations of this protocol include the use of a sole patient cohort and the risk of selection bias, which means that the results may not be generalised to other populations or settings beyond the selected clinical outpatient. Furthermore, reliance on self-reported dietary data through FFQs and 24-hour recalls introduces potential recall bias and measurement error, which may impact the accuracy of dietary assessments [52, 53]. Nonetheless, this study protocol presents several notable strengths. Firstly, the study will address a critical gap in the rising challenge of hypertension in Nigeria and the lack of a brief dietary tool that can be incorporated into clinical care by focusing on the feasibility, validity, and acceptability of a dietary assessment tool explicitly tailored to Nigeria. Secondly, the inclusion of both clinical patients and healthcare professionals in the feasibility assessment phase ensures comprehensive feedback from both user groups, enhancing the applicability and relevance of the dietary assessment tool. Thirdly, should the tool prove to be valid, it holds the potential for adaptation and application in other West African countries. This is attributed to the fact that the tool was crafted based on a food list derived from both Nigerian and Ghanaian national nutrition guidelines [7, 19], as well as findings from our comprehensive systematic review and meta-analysis [5].

In summary, although larger scale studies will be required in more diverse populations in Nigeria, this is a major step towards a culturally-informed dietary questionnaire for clinicians, patients, and researchers that will contribute towards dietary assessment and hypertension prevention in Nigeria.

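### The FFQ score takes its weights from p<0.05 items in 27 separate models fitted to about 17 patients, so the weights are likely to be unstable and inflated and a null Phase 2 result would be hard to interpret

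*Protocol article*

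**What the plan says.** The Abstract places derivation in Phase 1 ("During the analysis of Phase 1 data, a scoring system will be developed") and external testing in Phase 2 ("Phase 2 (n = 50) will assess the acceptability of the FFQ and validate the association between the FFQ score and hypertension"). For Phase 1 patients, Sample size and sampling technique states that "the target sample size will be increased to 50 participants". The 25 healthcare professionals add nothing to the derivation: "Healthcare professionals are not involved in the patient FFQ validation stage", and in Non-dietary data collection blood pressure "will be measured using a standard procedure from each clinical patient".

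Development of FFQ score sets out the method. Weights come from "using a random sub-sample of the study population (e.g., 1/3) as a test group". Intake of each of 27 items is cut into tertiles, and each item gets its own covariate-adjusted model. The integer-rounded coefficient of an item "in each multiple variable model, that is significant (p<0.05), will be used as a" weight. The score is then computed and tested in the remaining two thirds. Correlation matrices and forward stepwise regression are to deal with correlated items. A significant association is taken as evidence that the score is valid. No shrinkage, resampling or multiplicity control is described.

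The outcome is not the same throughout. Development of FFQ score uses hypertension for the item models. Study objectives and Statistical analysis use blood pressure, and Statistical analysis describes the derivation without a split.

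**The concern.** The rule combines three things that each make weights worse: a very small derivation group, a significance filter applied 27 times, and unshrunken coefficients used directly as weights. In a group of about 17, only an item with a very large observed association can pass the filter. Items with real but modest associations will mostly be missed, those that pass will be overestimated, and chance items will pass alongside them. Forward stepwise selection on the same patients adds further data-driven selection.

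Two of the five study objectives depend on this score, and the Abstract promises a validated tool. If Phase 2 then shows no association, the investigators could not say whether the questionnaire carries no information on blood pressure or whether the weights were poor.

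**Working it through.** **The only sample-size figure in the article.** It is N = 29 for r = 0.5 between FFQ and recalls (two-sided 0.05, power 0.8). Fisher z gives ((1.960 + 0.842)/0.549)² + 3 = 29.0. Exact power is just under 0.80 at 28 and 0.81 at 29. The figure is correct for its purpose, but it does not cover the score, and the derivation group is smaller than it.

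**Derivation size.** 50/3 = 16.7, about 17. With the article's 20% dropout it is 40/3, about 13.

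**Covariates (k).** The item models name sex and age as examples (k = 2). Statistical analysis lists five for the final score model (k = 5, one term each). Both are shown.

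**Threshold for keeping an item.** df = n − k − 2 and critical |r| = t/√(t² + df).
- k = 2: df = 13, t = 2.160, critical |r| = 0.51
- k = 5: df = 10, t = 2.228, critical |r| = 0.58

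**Power per item** (exact, effective sample size n − k; the first figure is k = 5, the second k = 2):

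| Derivation n | r = 0.2 | r = 0.3 | r = 0.5 |
|---|---|---|---|
| 17 | 0.09-0.11 | 0.16-0.19 | 0.40-0.50 |
| 25 (a half) | 0.13-0.15 | 0.25-0.29 | 0.64-0.71 |
| 50 (all) | 0.26-0.28 | 0.53-0.55 | 0.95-0.96 |

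**False items under the null.** 27 × 0.05 = 1.35 expected. The chance of at least one is 1 − 0.95^27 = 0.75 if the tests are independent.

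**False share of kept items.** With m truly associated items, the share is (27 − m) × 0.05 / [(27 − m) × 0.05 + m × power]. Example: m = 5, r = 0.3, k = 2 gives 1.10/(1.10 + 0.97) = 0.53. The values of m and r are assumptions. At n = 17:

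| True items | r = 0.2 | r = 0.3 |
|---|---|---|
| 3 | 79-81% | 67-72% |
| 5 | 67-70% | 53-58% |
| 9 | 48-51% | 34-39% |

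Three items at r = 0.5 give 44-50%. More true items lower the share further (13 at r = 0.2: 33-36%).

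**Simulated Phase 2 result.** Assumptions: 1,500 runs, independent items in tertiles, linear blood pressure with SD 20 mmHg, 2 covariates, p<0.05 selection, rounded weights, 50 new Phase 2 patients, stepwise step not modelled. Success means a significant positive association.

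| Assumed truth | Variance explained (m × r²) | Weight inflation, n = 17 | Score r, n = 17 | Success, n = 17 | Success, n = 50 |
|---|---|---|---|---|---|
| 5 items, r = 0.2 | 0.20 | 3.1-fold | 0.08 | 12% | 27% |
| 9 items, r = 0.2 | 0.36 | 3.1-fold | 0.13 | 21% | 48% |
| 5 items, r = 0.3 | 0.45 | 2.1-fold | 0.19 | 36% | 83% |
| 9 items, r = 0.3 | 0.81 | 2.1-fold | 0.31 | 60% | 98% |
| 3 items, r = 0.5 | 0.75 | 1.3-fold | 0.46 | 79% | 100% |

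The two most favourable rows need the foods to explain 75-81% of blood pressure variance. The last column keeps the p<0.05 rule, so its gain comes only from dropping the split.

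**Effect of penalisation.** In a separate simulation (10 of 27 foods linked, 0.15 SD of blood pressure per SD of intake), the out-of-sample r was 0.05 for the stated rule at n = 17, 0.11 for the same rule at n = 50, and 0.21 for ridge at n = 50.

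**Outcome scale.** If the item models are logistic, 17 patients give about 8 events on an even split, for at least 3 parameters plus an intercept. Any coefficient below 0.5 (odds ratio below e^0.5 = 1.65 per tertile) rounds to a weight of zero. On a mmHg scale rounding matters much less.

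**The case against.** Several points stand. The one third is given as an example, and the five-covariate case borrows a list meant for another model. Neither rescues the rule: half the patients with two covariates still gives power of only 0.29 at r = 0.3. Reading the study population as both phases (about 33 for derivation) gives 0.35-0.38 and conflicts with the Abstract. The score-hypertension association is a secondary outcome that the article says it will explore, and the Discussion calls for larger studies. That bears on severity, not on whether the rule is sound. The held-out two thirds and Phase 2 also guard against false confirmation, since a poor score would tend to fail there.

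A reader might go further and infer that the weights will be mostly noise, that the score cannot work, or that a null Phase 2 result would show the derivation method to be at fault. The article does not support this. It gives no item effects. In some of the assumed cases most kept items are real, and simulated Phase 2 success reaches 79%. A null result would be ambiguous between the two explanations; it would not point to one of them.

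Nor does the limitation about "the use of a sole patient cohort" show that the phases share patients. That sentence concerns generalisability.

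The fix has limits too. A score with a true r of 0.21 has about 31% power in 50 Phase 2 patients (Fisher z), so sample size remains the underlying constraint.

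**Conclusion.** The concern holds as a poorly chosen derivation rule that should be changed; it does not show that the score must fail. Certain from the text: about 17 patients at the stated example fraction, 27 uncorrected p<0.05 filters, and unshrunken rounded weights. Following by calculation: a keeping threshold of |r| 0.51-0.58, power below 0.20 per item at r = 0.3, and 1.35 expected false items under the null. Dependent on assumed effects: a false share of about a third to four fifths for 3 to 9 true items at r = 0.2-0.3, weights of true items inflated about 2- to 3-fold at those effects, and Phase 2 success from about 10% to 80%. The simulations assume independent items and a continuous outcome. Dropping the split raised the chance of Phase 2 success in every non-null case tried. The change is advisable before the score is derived, but the association is a secondary, exploratory outcome, so this is a should-fix.

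**What to change.** 1. Drop the one-third/two-thirds split and derive the score on all 50 Phase 1 patients.
2. Replace the 27 models and the p<0.05 filter with one penalised model, for example ridge, with covariates unpenalised, the penalty chosen by cross-validation and optimism reported by bootstrap.
3. Name one derivation outcome and reconcile Development of FFQ score with Study objectives and Statistical analysis. Continuous blood pressure matches the stated objective and avoids small logistic coefficients rounding to zero. If integer weights are wanted, state the scale on which they are rounded.
4. Freeze the score and validate it once in the 50 Phase 2 patients, none of whom may come from Phase 1.
5. Describe the score as exploratory.

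The cost is a rewritten paragraph, somewhat more analysis code and a recruitment condition for Phase 2; no extra patients are needed. The interim check in about 33 patients is lost. Phase 2 uses the refined FFQ, so the items that enter the score must stay comparable between phases. Taking weights by direction only from the earlier systematic review would avoid estimation, but it departs from the objective of deriving weights from this study's own associations, so it is not proposed here.

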### Study aims and objectives

#### Study aims

The overall aim is to deliver a clinically tested and validated short dietary assessment tool that will be ready to use by clinicians, patients, and researchers across Nigeria to provide personalised dietary advice to patients with hypertension and empower its citizens to improve their diet and take an active role in hypertension prevention.

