#### Intervention

*Food frequency questionnaire (FFQ)*. This study will use a 32-question semi-quantitative food frequency questionnaire (FFQ) designed to capture individuals’ usual food intake over the past month for 27 food groups. The list of commonly consumed foods was guided by the Nigerian and Ghana National Nutritional Guideline on Non-Communicable Disease Prevention, Control and Management [7, 19] and supported by our systematic review and meta-analysis regarding dietary factors associated with hypertension in the West African region [5]. The FFQ consists of 26 questions covering major food groups and an additional 6 questions on salt. These food groups encompass a diverse range of foods favourably or unfavourably associated with hypertension, including: fruit, vegetable, fibre-breakfast cereals, rice and pasta, beans, yam and potatoes, fried or fast foods, whole meat, white meat, processed meat, sugary fizzy drinks and fruits, diet non-alcoholic drinks, tea and coffee, soups and stew (fatty soups, vegetable soups, draw soups, native soups, and stews), nuts and seeds, dessert and sweets, fats and oils, salt, milk and milk-based beverages. For each food item, participants will report the frequency of consumption over the past month, with response options ranging from ’rarely or never,’ ’1–2 times/week,’ ’3–5 times/week,’ to ’daily,’ and ’more than once per day. We also acknowledge that the FFQ is likely to evolve as it is tested in more clinics and by more individuals across Nigeria.

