## Discussion

Unhealthy dietary shifts from whole foods to highly processed ‘fast food’ options have been linked to the escalating hypertension prevalence in Nigeria. Notably, dietary habits are evolving, marked by increased consumption of meals from eateries and fast-food vendors offering high-fat, high-salt, and high-sugar processed foods [1, 5, 6]. Positive outcomes in hypertension and cardiovascular health have been noted through dietary and lifestyle changes [39–42]. Hence, responsive short dietary assessment tools can swiftly guide healthcare professionals in pinpointing concerns and establishing and tracking dietary goals for patients, including patients with hypertension [43, 44]. Several tools exist for dietary management of cardiovascular disease, type 2 diabetes, hypertension, and non-alcoholic fatty liver disease (NAFLD) that have successfully been developed for clinical use [32, 43, 44]. Nevertheless, many of these tools have been designed and validated primarily in the US and Western European nations, limiting their applicability to Nigeria. Our primary aim is to explore the feasibility, validation, and acceptability of a short dietary assessment tool for evaluating dietary intake among individuals with hypertension in Nigeria.

Currently, no short dietary assessment tool responsive to dietary changes has been developed for hypertensive patients and incorporated into clinical care for the prevention and management of patients with hypertension in Nigeria. Given the practicality of FFQs in settings lacking formal dietetic support and their inherent inclusion of portion sizes to minimise measurement error [15], our aim is to validate a developed short FFQ. The developed FFQ will be informed by the findings of [name] et al. [5] and the Nigeria Nutritional Guidelines [10] culminated in a 27-item tool designed for use with hypertensive patients. We aim to investigate the relative validity of our newly developed short FFQ in relation to 24-hour dietary recall from 50 clinical patients focusing on commonly consumed food in Nigeria. This approach to validate the FFQ has been extensively utilised in the literature by previous studies [32, 45–48].

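### FFQ score: sample tertiles of a five-option frequency item, cut in about 17 patients, give empty or unequal groups and chance-driven boundaries, and the integer weights rest on an outcome scale that the article words in different ways

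*Protocol article*

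**What the plan says.** All references are to the protocol article.

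- **Response scale.** Under Intervention, "participants will report the frequency of consumption over the past month" on five ordered options, from rarely or never up to more than once per day. The instrument is called semi-quantitative, and "The FFQ consists of 26 questions covering major food groups and an additional 6 questions on salt".
- **Categorisation.** Development of FFQ score proceeds by "using a random sub-sample of the study population (e.g., 1/3) as a test group". In that group "the intake of all 27 food items for each participant will be converted into tertiles", which are labelled low, moderate and high intake.
- **Weights.** The same section fits one adjusted model per food group, 27 in all, against hypertension. It describes the weights as follows: "The beta-coefficients for the food item (rounded to the nearest integer"), kept only where p<0.05. The tertiles and weights are then applied to each individual in the remaining two thirds.
- **Outcome for the weights.** Development of FFQ score says hypertension and names no regression type. Study objectives says continuous measures, namely blood pressure. Statistical analysis says blood pressure. Logistic regression is named only for testing the finished score in Phase 2.
- **Purpose.** Study aims wants a tool "ready to use by clinicians, patients, and researchers across Nigeria".

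**The concern.** Tertiles assume a variable with enough distinct values to be cut into thirds. A five-option item in about 17 people often cannot be cut that way, because many patients share an answer and a whole block of ties must fall on one side of a boundary. A group can then be empty or hold most of the sample, and the model no longer compares low, moderate and high intake.

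The boundary also becomes a product of the draw. Whether three to five times a week counts as moderate or high would depend on which patients happened to enter the test group, and that accident would be built into a score intended for national use.

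The weights have a related weakness. Rounding a raw coefficient to an integer means something different in mmHg than on the log-odds scale, and the article words the outcome for this step in more than one way.

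**Working it through.** **The plan's own figure.** The article computes no figure for the score. Its one computed figure is the minimum of 29 patients for FFQ versus recall agreement (r = 0.5, two-tailed alpha 0.05, power 0.8). Fisher's z gives ((1.960 + 0.842)/atanh 0.5)² + 3 = 29.01, and simulated power is 0.799 at n = 28 and 0.815 at n = 29. The 29 reproduces, but it does not bear on the score.

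**Inputs.** From the article: five options per item, 27 food groups, a test group of about 1/3, and 50 Phase 1 patients, so 50/3 ≈ 17. If both phases were pooled (assumption), 100/3 ≈ 33. The response distributions are assumed, because the article gives none. Percentages in the five options, ordered from the most to the least used:

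- even: 20/20/20/20/20
- mild skew: 30/30/20/12/8
- half in one option: 50/25/15/6/4
- 60% in one option: 60/20/12/5/3
- 70% in one option: 70/17/8/3/2

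**Step 1: do three groups form?** Cut at the sample 1/3 and 2/3 quantiles, with values tied at a cut going to the lower group, over 20,000 draws. With quantiles taken as observed values:

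| Distribution | Empty group, n=17 | Largest group ≥50%, n=17 | Empty group, n=33 |
|---|---|---|---|
| Even | 13% | 42% | 3% |
| Mild skew | 10% | 52% | 9% |
| 50% in one option | 11% | 61% | 5% |
| 60% in one option | 28% | 83% | 28% |
| 70% in one option | 61% | 96% | 73% |

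With interpolated quantiles, the range for an empty group at n = 17 widens to about 10–78%. At the low end, 27 × 0.10 ≈ 2.7 items would be expected to lose a group in any one test sample.

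**Step 2: are the boundaries stable?** Draw two independent test groups of 17 from the same population, cut each, and compare where the five options fall. At least one option changes tertile in about 35–78% of draws per item. Weighted by how many people choose that option, about 5–24% of persons are reclassified. Other assumed inputs put the upper end at about 27%.

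**Step 3: what does integer rounding do on each scale?** Enter the tertile as 1, 2, 3 (variance 2/3) and find the smallest coefficient that passes p<0.05.

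- *mmHg, assumed SD 15–20.* Threshold = t(0.975, n−4) × SD/√(n × 2/3). At n = 17 and SD 15, 2.16 × 4.46 = 9.6; at SD 20, 12.8. At n = 33 it is 6.5–8.7. A rounding error of at most 0.5 on 9.6 is about 5%.
- *Log-odds, assumed hypertensive share p of 0.5 to 0.3.* Threshold = 1.96/√(n·p(1−p)·2/3). At n = 17 and p = 0.5, 1.96/√2.833 = 1.16; at p = 0.3, 1.27. At n = 33 it is 0.84–0.91. Retained weights become small integers: 1.4 rounds to 1, a loss of 0.4/1.4 = 29%.

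The same rounding rule is therefore nearly neutral in mmHg and coarse in log-odds.

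**The case against.** Four points can be made for the plan.

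1. **The collapse is conditional.** It rests on assumed distributions. The Discussion credits FFQs in general with "inherent inclusion of portion sizes to minimise measurement error", and the salt group has six questions, so some items may take more than five values. This stands as a limit on the size. However, Intervention describes only frequency responses, and even the evenly spread distribution gives unequal groups often.

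2. **A reader might infer that a single clinic patient cannot be scored.** The article does not support that. It applies the test-group tertiles and weights to other individuals, and a boundary on a five-option item is an option boundary that can be applied to one person. For the same reason, disagreement between tertiles cut separately in the two groups is not relevant here. What remains is that the carried-forward boundary is unstable.

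3. **A reader might infer that rounding wipes out significant foods with log-odds below 0.5.** That is correct arithmetic but has no effect here. The p<0.05 filter in the same sentence already removes such coefficients; one could be significant only with a test group of about 92–110. In 1,500 simulated adjusted logistic fits per setting, the smallest significant coefficient was 1.38 at n = 17 and 0.87 at n = 33. Nor does the article say that the weights are log-odds.

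4. **Tie handling, numeric cut-points and scaling are details that an article leaves to the full plan.** This is fair, and their absence is not the point. The use of sample tertiles, the integer rounding and the differing outcome wording are all stated in the text.

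**Conclusion.** The point holds in this form. Sample tertiles of a five-option item in about 17 patients are a poor choice that the article fixes explicitly. At n = 17 an empty group occurs in about 10–78% of draws per item, boundaries differ between two random test groups in about 35–78% of draws, and about 5–24% of persons are reclassified. Pooling both phases to about 33 does not cure it for skewed items.

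The integer weights also depend on an outcome that is worded as hypertension in one section and as blood pressure in two others. The two blood pressure statements suggest that mmHg is intended, and on that scale rounding is minor, so this part is mainly a matter of reconciling the wording.

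The sizes rest on the assumed response distributions and tie rules, a hypertensive share of 0.3–0.5, a blood pressure SD of 15–20 mmHg, and tertiles entered as 1, 2, 3.

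**What to change.** In Development of FFQ score:

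- Replace the sample tertiles with the questionnaire's own response options, scored 0–4, or collapsed into three groups at the same stated frequencies for everyone.
- State that this one table is applied unchanged in the validation group and in Phase 2.
- State that the weights come from the continuous blood pressure model described in Study objectives and Statistical analysis.
- Divide all retained coefficients by one common constant, such as a fixed number of mmHg, before rounding.

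The cost is wording only; no extra data are needed. The downside is that groups will not be equal in size within the sample, so rarely used options will carry little information. The change does not make weights estimated in about 17 patients any more precise; it removes the additional instability that comes from the cut-points.
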